#### Tertiary

Using the SES-SFV, forced sexual contact will have occurred when a participant answers one of three questions indicating she had experienced threatened, forced, or drug facilitated non-consensual sexual touch not including intercourse (e.g., “fondled, kissed, or rubbed up against the private areas of my body (lips, breast/chest, crotch or butt) or removed some of my clothes”). Sexual coercion will have occurred when a participant reports one or more incidents of verbally coerced (e.g., “threatening to spread rumors about me”, “continually verbally pressuring me after I said I didn’t want to” -- excluding threats of physical harm) non-consensual oral, vaginal, or anal intercourse.

### Proposed methods for protecting against sources of bias

#### Selection bias

Selection biases are evident in all studies and programs with a sexual or sexual violence theme because they disproportionately attract more sexually experienced and sexually victimized participants [84]. Similar selection biases are in effect when voluntary rape programming is offered on campuses. The internal validity of our intervention is high, and therefore selection biases are not likely to have a strong influence on the outcomes. Selection bias will be assessed by comparing the sample to the entering student demographic data.

#### Outcome assessment bias

Blinding is not possible in this trial. However, bias in outcome assessment is addressed by having the primary outcome, sexual assault, collected with the best measure of coercive sexual experiences available [SES-SFV, 71]. This measure will be applied equally to all study participants. Previous versions of the measure have been tested on tens of thousands of undergraduate students and it has high reliability and validity [72,85]. The 2007 scale corrects weaknesses in the earlier version. Although the SES-SFV is not an ‘objective measure’ of sexual assault, since no external adjudication is possible, it is the best option available. The instrument does not ask about the occurrence of sexual assault or coercion directly but rather asks how often a particular behaviour occurred (e.g., “A man put his penis into my vagina, or inserted fingers or objects without my consent by using force, for example holding me down with his body weight, pinning my arms, or having a weapon”).

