## Methods/Design

### Study design

This is a multicentre randomized controlled trial. By necessity, the design will be open-label, whereby the participants will be aware of the nature of the assigned sexual assault intervention. There is no evidence from our pilot testing that knowledge of the assignment influences participants’ responses on key outcomes in any way. For example, post-randomization pre-intervention scores did not differ between participants who were assigned to the AAA education programs and those assigned to no-program.

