### Interventions

#### Control condition: University-provided brochures

To match the current ‘standard of care’ at Canadian universities, participants will be invited to take and read brochures on sexual assault selected from those available on their Canadian university campus. It is not possible to provide identical brochures across all three sites as each contains city-specific community services and sexual assault hotlines. However, the content of the brochures regarding sexual assault are similar and all sites’ brochures include general information on sexual assault and ‘date-rape’ drugs and post-rape legal and medical advice. One of two research assistants at each site will conduct each session, asking the participants to take brochures they are interested in, read them over, and ask any questions they may have. Questions will be answered in a group setting or individually if a participant stays after other participants have left to ask their question privately. Interaction between participants and the research assistant on the topic will be limited to 10–15 minutes after all preliminary activities (e.g., settling, getting food or beverages) are completed and will be audio recorded for verification.

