### Assessments

At baseline, participants will complete computerized surveys prior to being randomized. They will then go immediately to their first intervention session, either to receive their brochures or to attend their first educational unit. To assess knowledge acquisition, intervention participants will have their 1st follow-up assessment 1 week after the last intervention session with control participants matched to the same interval. Subsequent follow-up assessments will occur at 6, 12, 18, and 24 months from the date of randomization. We will measure outcomes using in-person computerized surveys at baseline and 1 week after the last intervention session. All other follow-ups will use secure web-based surveys linked only by participant codes to protect privacy.

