(c) Knowledge of effective rape resistance strategies will be measured by identification of a greater number of forceful physical and forceful verbal strategies in response to threatening hypothetical situations (*Resistance measure*, [79]) and real situations (items requesting details following sexual assaults experienced, questions added to SES items, [48]). Testa et al.’s [79] measure follows a scenario depicting an interaction where the participant is on a date with “an attractive man” (p. 666). These items about the participant’s “intended behaviour” break down into 3 subscales: direct-resistance, polite-resistance, and passive-response. The direct-resistance subscale, which is our focus, has high internal consistency ranging from 0.89 to 0.94 and validity demonstrated by the authors. Additional, added questions, “If a man I knew (e.g., a date) tried to force me to have sex with him when I didn’t want to, I would …”, If a stranger tried to force me to have sex with him when I didn’t want to, I would …” were pilot tested to ensure clarity and consistency of coding of responses. Scoring is based on Ullman’s [45] study of the tactics used by women who avoided completed rape and has high inter-rater reliability (Cohen’s kappa > 0.90).

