#### Differential drop out

Our pilot study indicated that dropouts are minimized by having follow-up times coincide with the school year rather than with holiday breaks. Based on Dillman [86] we will make up to 4 reminder phone calls/e-mails following confirmation of contact at follow-up. Further, web-based survey administration makes completion of surveys easier for participants, as measured by our low drop-out rate (3 mo, 0%; 6 mo 11%) in the 2007/2008 pilot study. A research assistant at each site will be hired to phone and e-mail participants to complete follow-ups. For students who do not wish to continue in the study, we will administer a 5-minute telephone version of the SES-SFV at 1-year and 2-years so we can ascertain their sexual assault status. Taken together, these methods will reduce the drop-out rate considerably.

There is a possibility that women in the control arm may not feel as connected to the trial, and may drop out as a result. Our pilot data are suggestive of this possibility. We have reduced the likelihood of differential drop out by providing a small intervention (brochure) rather than using a no-contact control, by providing incentives and personalized phone contact, as well as offering the opportunity for control participants to receive the full program at the end of the trial. These maneuvers will maximize connection to the trial and will reduce differential attrition.

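### The statement that blinding is impossible is too broad: staff who code open-ended answers and staff who take the telephone SES-SFV could be masked

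*Protocol article*

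**What the plan says.** The protocol article deals with blinding in two places. *Study design* gives a reason that concerns participants: "By necessity, the design will be open-label, whereby the participants will be aware of the nature of the assigned sexual assault intervention". *Outcome assessment bias* then drops the restriction: "Blinding is not possible in this trial". The protection offered there is a well-validated instrument, applied equally to everyone.

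Most outcome data are self-completed. Baseline and 1-week surveys are done on computer in person, and for the rest *Assessments* says "All other follow-ups will use secure web-based surveys linked only by participant codes to protect privacy".

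Two outcome steps are handled by staff:

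- **Coding.** Secondary outcome (c) includes added sentence-completion items on what a woman would do if a known man or a stranger tried to force sex. These "were pilot tested to ensure clarity and consistency of coding of responses". The control named is inter-rater agreement, with kappa above 0.90.
- **Telephone ascertainment.** For women who do not wish to continue, *Differential drop out* says "we will administer a 5-minute telephone version of the SES-SFV at 1-year and 2-years so we can ascertain their sexual assault status".

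On staff roles, *Randomization* has the research assistant obtain each allocation from the website. For the brochure arm, "One of two research assistants at each site will conduct each session". *Differential drop out* adds that a research assistant will be hired at each site to telephone and e-mail participants for follow-up. The article does not say whether that person is separate from the staff who randomize and run sessions.

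**The concern.** The unqualified sentence stands in the section on outcome assessment, where masking of assessors would normally be settled. It rules out masking for every role, while the reason given covers only participants. This is therefore more than a detail left to a fuller protocol: the article makes a positive statement that is wrong for some roles.

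For the coding step, a high kappa shows that raters agree with one another. It does not show that they are free of a tilt they share because they know the arm. The items ask about forceful resistance, which is what the program teaches, so a rater who knew the arm would also know which answers to expect.

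For the telephone step, the one-year call can decide whether a woman counts as having had the primary event. An interviewer who knew the arm could affect prompting, tone or recording. If telephone use differed by arm, so would exposure to that influence. The article raises this possibility when it says that "women in the control arm may not feel as connected to the trial, and may drop out as a result".

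**Working it through.** **Who can be masked, role by role**

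| Role | Where described | Can it be masked? |
|---|---|---|
| Participant | *Study design* | No; reason given |
| Facilitator | *Interventions* | No; delivers the program |
| Assessor for self-completed surveys | *Assessments* | No; the participant is the assessor |
| Coder of open-ended items, outcome (c) | *Outcome measures, Secondary* | Yes; data can be passed on by code number |
| Telephone SES-SFV interviewer | *Differential drop out* | Largely; a woman may reveal her arm |

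The sentence holds for the first three rows and not for the last two.

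**The plan's own figures**

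Inputs from *Sample size considerations*: 25% v 17.5%, two-sided 5%, 80% power, design effect 1.38, division by 0.75.

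- Pooled-variance formula: n = [1.960 × √(2 × 0.2125 × 0.7875) + 0.842 × √(0.25 × 0.75 + 0.175 × 0.825)]² ÷ 0.075² = 465.8, so 466 per group and 932 in all, as stated.
- Design effect: 1 + 19 × 0.02 = 1.38.
- Total: 932 × 1.38 ÷ 0.75 = 1714.9, against 1716 stated, which is close enough.

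Masking changes none of these figures. They serve only as the scale for what follows.

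**How much arm-aware calling could matter**

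The article gives no telephone share. The 10% first-year loss does not supply one, because it counts women whose status cannot be ascertained, and a telephoned woman is ascertained. The following are therefore assumptions:

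- the true rate is 25% in both arms (no effect);
- there are 466 effective women per arm;
- a share f of women is ascertained by telephone;
- callers under-record events in the program arm by a relative amount d.

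The spurious difference is Δ = 25% × f × d. The observed program rate is p = 25% − Δ, with standard error SE = √[(0.25 × 0.75 + p(1 − p)) ÷ 466]. The two-sided type I error is 1 − Φ(1.96 − Δ/SE) + Φ(−1.96 − Δ/SE).

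| f | d | Δ (points) | Share of 7.5 points | Type I error |
|---|---|---|---|---|
| 5% | 10% | 0.13 | 1.7% | 5.0% |
| 10% | 20% | 0.50 | 6.7% | 5.4% |
| 15% | 30% | 1.13 | 15% | 6.8% |
| 25% | 30% | 1.88 | 25% | 10.3% |

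The middle rows move the result little. The last row needs a quarter of women to be telephoned and a strong caller effect in one arm only.

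No comparable figure can be given for outcome (c), because the article states no expected effect for it.

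**The case against.** The strongest reply is that the sentence, read in context, is close to correct. *Study design* ties the open label to participants, and *Outcome assessment bias* goes straight on to a self-reported primary outcome that cannot be adjudicated externally. For the main route, web self-completion, no staff assessor exists. Who codes, who calls and what they can see are operating details that an article often leaves to the full protocol. Survey data are already linked by code, so coders may in fact work without the arm, and the hired follow-up assistant may be a separate person. The SES-SFV items are closed and behaviour-specific, which limits a caller's room to shift answers. The open-ended items are one component of one of five secondary outcomes, alongside a structured subscale.

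Much of this stands, and it keeps the point modest. It does not rescue the sentence, which denies the possibility of blinding where silence would have left the matter open.

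Four stronger readings are tempting, and the document does not support them:

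- *That coders and callers know the arm.* This would be an inference from research assistants' other duties. The article does not say so.
- *That the plan expects more drop-out among controls.* It calls this a possibility, describes the pilot data as suggestive, and lists measures against it.
- *That lower disclosure by telephone is part of this problem.* That is a mode effect, and masking callers would not cure it. For scale, assume 15-20% of controls and 5-10% of program women telephoned, with disclosure 10-30% lower. A true 25% v 17.5% would then appear as 6.3 points (23.50 v 17.24, RR 0.73) to 7.3 points (24.63 v 17.33, RR 0.70), which is towards the null.
- *That masking callers by exchanging call lists between sites costs almost nothing.* It would move contact details and disclosures of withdrawn women between universities with separate ethics approvals, and could weaken the personal contact on which retention relies.

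**Conclusion.** The point holds as a correction of scope. Blinding is impossible for participants, facilitators and self-completed surveys. Nothing in the article shows it to be impossible for coders of the open-ended items or for telephone interviewers, and no separation of those staff from allocation is stated.

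The likely effect on the primary outcome is small: about 0.1-1.9 points under the assumed telephone shares and one-arm under-recording, and toward the upper end only if many women are telephoned. A reader might infer that the primary result is seriously threatened, but the document gives neither a telephone share nor evidence of arm-aware calling that would support this. The coding limb affects secondary outcome (c) only. Masking these staff would leave the larger bias, unblinded self-report, where it is. The change is still worth making, because it removes an avoidable source of bias without touching sample size, alpha or treatment.

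**What to change.** 1. **Limit the sentence.** For example: participants and facilitators cannot be blinded; coders of open-ended responses and telephone interviewers will be kept unaware of allocation. If either group cannot be masked, say why.
2. **Coders.** Supply responses by code number only, without arm or session. This can be done whenever the text is coded.
3. **Telephone SES-SFV.** Have the follow-up assistant already to be hired at each site make scripted calls, with no access to allocation and no role in randomization or sessions. No call lists need pass between sites.
4. **Sensitivity analysis.** Keep telephone responses in the primary analysis, and repeat that analysis with them treated as missing. A difference between the two would not isolate caller bias, since it would also reflect survey mode and the kind of women who withdraw.

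**Cost.** Removing the arm from the coding file is trivial. Keeping the caller's role separate constrains staffing at each site. Some women will reveal their arm on the telephone, and some written answers will suggest it, so masking will be incomplete. At the time of the article 918 of 1716 women had been enrolled, so any calls already made cannot be masked in retrospect. Later ones can be.

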#### Differential drop out

Our pilot study indicated that dropouts are minimized by having follow-up times coincide with the school year rather than with holiday breaks. Based on Dillman [86] we will make up to 4 reminder phone calls/e-mails following confirmation of contact at follow-up. Further, web-based survey administration makes completion of surveys easier for participants, as measured by our low drop-out rate (3 mo, 0%; 6 mo 11%) in the 2007/2008 pilot study. A research assistant at each site will be hired to phone and e-mail participants to complete follow-ups. For students who do not wish to continue in the study, we will administer a 5-minute telephone version of the SES-SFV at 1-year and 2-years so we can ascertain their sexual assault status. Taken together, these methods will reduce the drop-out rate considerably.

There is a possibility that women in the control arm may not feel as connected to the trial, and may drop out as a result. Our pilot data are suggestive of this possibility. We have reduced the likelihood of differential drop out by providing a small intervention (brochure) rather than using a no-contact control, by providing incentives and personalized phone contact, as well as offering the opportunity for control participants to receive the full program at the end of the trial. These maneuvers will maximize connection to the trial and will reduce differential attrition.

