#### Lost to follow up

Lost to follow-up will be defined as not being able to ascertain a woman’s sexual assault status at 1 year. Our 6-month pilot study had less than 5% of participants moving or changing their phone numbers or e-mails without updating their information with the Registrar or contacting the researchers, and therefore being ‘lost to follow up’. The primary outcome for the present trial is at 1 year rather than at 6 month follow-up, and therefore we have doubled the estimated rate of lost-to-follow-up to 10%. We expect a loss of no more than another 15% at the end of the second year of follow-up. Our lost-to-follow-up numbers are reasonable based on recent estimates that less than 25% of students drop out of university by the end of their second year [87].

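### The short telephone SES-SFV is tied to women who do not wish to continue; it should also reach enrolled, contactable women who have not returned the 12- or 24-month survey

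*Protocol article*

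**What the plan says.** - **Mode of the survey.** Baseline and 1-week assessments are in person. For the rest, Assessments says: "All other follow-ups will use secure web-based surveys linked only by participant codes to protect privacy".
- **Chasing non-returners.** Differential drop out says: "we will make up to 4 reminder phone calls/e-mails following confirmation of contact at follow-up". It adds: "A research assistant at each site will be hired to phone and e-mail participants to complete follow-ups". The Compliance section adds letters, secondary phone and e-mail details, at least two collateral contacts, and a $30 gift certificate for survey completion.
- **The fallback.** Differential drop out says: "For students who do not wish to continue in the study, we will administer a 5-minute telephone version of the SES-SFV at 1-year". It is repeated at two years, and its stated purpose is to establish these women's sexual assault status.
- **What counts as lost.** Lost to follow up says: "Lost to follow-up will be defined as not being able to ascertain a woman’s sexual assault status at 1 year".
- **Basis of the 10%.** The same section reports that the 6-month pilot "had less than 5% of participants moving or changing their phone numbers or e-mails" without the change being traceable. It doubles that figure to 10% at one year.
- **Non-response.** Compliance defines this for the secondary-outcome surveys.

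**The concern.** The fallback exists to obtain the primary outcome, yet its stated recipients are women who do not wish to continue. A woman who never says so, but does not complete the 12-month survey, gets repeated prompts towards the full web survey and no stated offer of the short form. If no event is already on record for her, her one-year status is unknown and she is lost by the article's own definition. The purpose given for the fallback applies to her just as much.

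At stake is bias in the primary comparison. Statistical analyses itself says that loss threatens validity when it is related to sexual assault and differs between groups. Differential drop out raises higher control-arm drop-out as a possibility and calls the pilot data suggestive of it. The planned multiple imputation assumes data missing at random, and the Cox model censors at last contact. Neither repairs loss that depends on the unobserved outcome. Collecting the outcome does.

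**Working it through.** **1. The plan's own sample size.** Inputs from Sample size considerations: 25% versus 17.5%, two-sided 5%, 80% power, intracluster correlation 0.02, cluster size 20, total attrition 25%.

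The pooled-variance formula is n per arm = [1.960·√(2·p̄·(1−p̄)) + 0.842·√(p₁(1−p₁) + p₂(1−p₂))]² / (p₁−p₂)², with p̄ = 0.2125.
- n = [1.960·√0.3347 + 0.842·√0.3319]² / 0.075² = 466 per arm, 932 in total. This matches.
- Design effect = 1 + 19 × 0.02 = 1.38.
- 466 × 1.38 / 0.75 = 857.4, rounded up to 858 per arm, or 1716. This matches.

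**2. Is power at risk from loss as such?** Effective n per arm at one-year loss L is 858(1−L)/1.38. Power at 25% versus 17.5%, with loss unrelated to risk:

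| One-year loss | Effective n per arm | Power |
|---|---|---|
| 10% (planned) | 559.6 | 86.7% |
| 16% | 522.3 | 84.3% |
| 21% | 491.2 | 82.0% |
| 25% | 466.3 | 80.0% |
| 30% | 435.2 | 77.3% |

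The 25% allowance covers both years, so the one-year analysis has a reserve. The head count is not the problem.

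**3. Is bias at risk?** Suppose a fraction m of an arm has unknown status, and these women have k times the risk of the observed women. The analysis uses women with known status. The observed rate is then p/(1 − m + m·k). The values of m and k below are assumptions; the documents give neither by arm.

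| Control loss | Program loss | k | Observed rates | Difference | Relative risk |
|---|---|---|---|---|---|
| 11% | 11% | 1 | 25.0% vs 17.5% | 7.5 | 0.70 |
| 11% | 11% | 1.5 | 23.7% vs 16.6% | 7.1 | 0.70 |
| 16% | 5% | 1.5 | 23.1% vs 17.1% | 6.1 | 0.74 |
| 16% | 5% | 2 | 21.6% vs 16.7% | 4.9 | 0.77 |
| 10% | 5% | 1.5 | 23.8% vs 17.1% | 6.7 | 0.72 |

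For row three: 0.25/(1 − 0.16 + 0.16 × 1.5) = 0.25/1.08 = 0.2315; 0.175/(1 − 0.05 + 0.05 × 1.5) = 0.175/1.025 = 0.1707; difference 0.0607. The last row lowers control loss from 16% to 10%: 0.25/1.05 = 0.2381, less 0.1707, is 0.0674.

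Equal loss leaves the relative risk at 0.70 even when missing women are at higher risk. The ratio moves when loss differs by arm. In row three power is about 72%, against 84.3% for an unbiased 16% loss in both arms. That fall comes mainly from the smaller observed difference.

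**4. Can the number of reachable non-returners be estimated?** Not reliably. The 11% non-completion at 6 months belongs to the 2007–2008 pilot, which had 32 students (0.11 × 32 ≈ 3.5 women). If the under-5% figure comes from that pilot too, it is fewer than two women (0.05 × 32 = 1.6). If it comes from another pilot, subtracting one from the other means nothing.

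**The case against.** The article does not say that withdrawers are the only recipients, and it does not abandon the others. They are phoned, e-mailed, written to, sought through collateral contacts and paid for completion. A woman who declines the survey on such a call could reasonably be handled as not wishing to continue. The exact trigger after the last reminder may also sit in a fuller operational document.

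Part of this stands. A reader might infer that silent non-responders get nothing; the Compliance section shows otherwise. What they lack is a stated short-form offer. The appeal to condensation is weaker, because the article does set the fallback's instrument, length, mode, timing and recipients, and the recipients are narrower than its purpose. Leaving the gap to each caller's judgement makes ascertainment of the primary outcome discretionary in an open-label trial. It also misses women who ignore reminders or keep promising to finish.

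Three other stronger readings fail:
- **That reachable non-returners are the larger group.** The article calls the 11% a drop-out rate, so it may include declared withdrawers, and the pilot was very small. Nor can the planned 10% be split into reachable and unreachable women, because it was built from uncontactable women alone.
- **That these women necessarily lose their primary outcome.** An event reported at 6 months already settles one-year status. The SES-SFV covers the time since the previous measurement and records the month of occurrence, so an 18- or 24-month survey could fill the gap for the final analysis. It would not do so in time for the analysis planned once one-year follow-up is complete.
- **That higher control-arm loss is expected.** The article calls it a possibility and lists countermeasures.

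**Conclusion.** The point holds as a narrowly drawn rule that is cheap to widen. It is neither a contradiction nor an arithmetic error. No section offers the short form to enrolled, reachable women who have not returned the 12- or 24-month survey, although the article's definition counts them as lost at one year unless their status is already known.

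The size cannot be fixed from the documents. Under the assumed 16% versus 5% loss and 1.5-fold risk, the difference shrinks from 7.5 to about 6.1 points, and reducing control loss to 10% restores about 0.6 of the 1.4 points lost. This takes all missing women as having no event on record and the same risk multiple in both arms. The fall in control loss is itself assumed, because no response rate to the short form is given. If loss is balanced, the relative risk is unaffected. If loss is unrelated to assault, there is no bias and power holds at 80% or more up to 25% one-year loss.

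**What to change.** In Differential drop out, replace the trigger for the short form with wording such as: every woman with no completed SES-SFV for the 12- or 24-month assessment after the fourth reminder is offered the SES-SFV-only short form, whether or not she has withdrawn, unless she has refused further contact. State that the trigger and procedure are the same in both arms, and record the mode of completion for each woman.

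The cost is mainly protocol wording, since the instrument and the site callers are already planned. The downsides are one more contact attempt, some secondary scales lost when a woman takes the short form instead of finishing the full survey late, and some mixing of web and telephone answers. Recording the mode allows that mixing to be examined.

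No change to the order of survey items is needed. The article states no order that is at fault, and putting the SES-SFV first could prime the risk-perception and rape-belief scales.
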